#### Same source/different method

The 2-day bladder symptom diary was developed by the PLUS consortium as an expanded version of a voiding record assessing storage symptoms (frequency, continence, sensation of urge and pain) and emptying symptoms (initiation, flow, efficacy, relief of urge sensation and pain) along with fluid intake and absorbent product usage over 2 days (Additional file 1). It is completed by a subset of women recruited from the general population and by all clinical center recruited women. The 1-day frequency/volume diary (Additional file 2) is being used to collect voided volume, frequency of urination, presence and severity of urinary leakage episodes, pad usage and fluid intake, and is completed only by clinical center recruited women.

#### Different source/different method

The inferential utility and validity of the PLUS-BHS will in part be determined by its comparability, as a measure of self-reported bladder health to what are deemed standard clinical judgements of bladder health. In order to capture this clinical judgement or rating of bladder health, each clinical research center has designated a variety of bladder health raters (a.k.a. judges). These judges are health care providers with a point of view which makes their clinical observation of bladder health a viable standard which can be used as a criterion. All women recruited for the clinical center populations meet with a judge who provides an overall bladder health assessment. For purposes of this study, a judge is considered a health care provider who is able to respond to basic questions or statements about the bladder from a participant. Operationally, we consider any provider (e.g., nurse practitioner, physician assistant, nurse midwife, physician, or surgeon) in family practice, internal medicine, geriatrics, obstetrics-gynecology, midwifery, urology, with or without subspecialty training in female urologic conditions. This design is expected to provide heterogeneity among judges and ensure generalizability that would not be possible using standardized evaluation procedures or only bladder specialists. This study also includes a balanced proportion of judges who are and are not engaged in the PLUS consortium, in order to minimize biases related to having heightened awareness of bladder health as a PLUS Consortium member.

Following the in-person interview with the participant, the judge provides two initial unaided ratings of bladder health: a circumstance or context adjusted, “relative” rating of bladder health as well as an “absolute” rating of bladder health (Additional file 3). No specific script or checklist for this rating is mandated; each judge may use whatever method they generally employ in their practice to assess their patients relative to bladder health. Along with each numerical rating (0–10), the judge is asked to provide the 3 most important factors that contribute to the rating. Following the completion of these initial ratings, the judge is provided with the participants 1-day frequency-volume bladder diary as well as the clinical test results (described below) and any other data available from standard of care clinical practice gathered during the interview process. This material is used by the judge to inform a second set of “relative” and “absolute” bladder health ratings along with the description of the 3 most important factors that contributed to each rating. Where practically feasible, the participant-judge interaction is scheduled to occur prior to the administration of clinical tests in order to minimize potential for test effect influence on participant’s interaction with the judge.

#### Different independent source/different method

Clinical tests completed during the in-person visit are measures that qualify as independent and objective data sources that provide evidence for a higher level of inferential validity. These tests are outlined in Table 4. In-person clinical measures included a quantified standing (provocative) paper towel test (PTT) for stress incontinence [38]; a non-instrumented, seated uroflowmetry with a minimum pre-void volume measurement of 150 mL assessed by bladder scan to determine volume, speed of flow, pattern and length of voiding; a non-invasive post-void residual (PVR) volume measurement by bladder scan; and a chemical urine analysis (a.k.a. dipstick) recording pH, specific gravity, blood, glucose, protein, leukocyte and nitrites to asses hydration status, infection and hematuria.

### Analysis plan

Item distributions will be evaluated for floor and ceiling effects. Items that exhibit greater than 85% response in the tail of the distribution will be removed. Item non-response will be evaluated with items demonstrating greater than 20% non-response considered for removal. Test–retest reliability will be evaluated for all items comparing item response on initial PLUS-BHI completion to item response on retest version of PLUS-BHI using Bland–Altman with 95% interval agreement threshold will be used for comparison of continuous variables (including categorical variables with greater than 6-point response options), and chi-square used for comparison of categorical variables, with Fisher’s exact used as needed.

A comparison of responses by mode (PAPI vs. CASI) will be made both between and within responses from the general population sample and the clinical samples separately. Items will be evaluated using Tukey’s HSD or chi-square (Fishers as needed). Items demonstrating significant differences across mode of administration or across sample will be considered for removal.

Internal dimensional validity will be identified and evaluated using factor analytic approaches. Two investigators utilizing multiple methods principal component analysis and factor analysis and rotation methods (orthogonal/oblique) will work independently and periodically compare and discuss results. Internal consistency of item groupings will be evaluated with Cronbach’s alpha. Item groupings with alpha > 0.9 will be further evaluated to determine whether items within grouping are, in reality, subtle variations of the same question. Item groupings with alpha < 0.4 will be rejected. Several criteria will be applied in evaluation of dimensions and factor retention: the Kaiser-Guttman rule (Eigenvalues > 1.0), factor loading thresholds of 0.60/0.40, scree plots, Kaiser–Meyer–Olkin (KMO) residuals off-diagonal partial correlations measure of sampling adequacy > 0.70 [28, 39, 40]. This analysis will be iterative. Emergent factor structures across mode and sample will be compared with the aim of identifying factor structures that are consistent across mode and across sample. The postpartum sample data will be evaluated similarly, with comparison of the factor structure made to final factor structure from general population sample and general clinical sample.

Our evaluation of levels of evidence is based on the work of Campbell and Fiske’s Multitrait-Multimethod (MTMM) matrix relative to the use of multiple-operationalism (multiple items to assess the range of a concept) to evaluate and establish levels of validity, although we use the term “dimension” in lieu of “trait.” [31]. Correlation values across multiple data sources and methods within each emergent dimension (factor) populating the MTMM matrix will allow evaluation of convergent validity and divergent validity.

Sample sizes are based on ensuring sufficient numbers of item response to conduct factor analysis. We aim to enroll the number of women necessary to achieve 10 participants per PLUS-BHI item included in the dimensional analysis [41], although less conservative estimates of 5–10 participants per item have been suggested [42]. Based on a maximum of 90 items a participant may respond to, our target number of completed BHIs in the general population sample (n = 694) and the clinical sample (n = 354) provides 8 and up to 12 participants per item evaluated, dependent on merging samples. This estimate is also conservative in that it accounts for all branching and not all participants will indeed branch based on their responses.

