**Fig. 1 Fig1:**
[figure not shown]
General population study flow. BHI, Bladder Health Instrument; CASI, Computer Assisted Self Interview; PAPI, Paper and Pencil self-Interview; RA, Random Assignment

Respondents, regardless of initial mode assignment, who fully complete the validation survey packet are subsequently re-contacted within 2–4 weeks and randomized 2:1 to complete either (a) a retest of the PLUS-BHI in the same mode (PAPI or CASI) followed by a 2-day bladder symptom diary (Additional file 1) or (b) to only complete a 2-day bladder symptom diary. The retest version of the PLUS-BHI includes 2 Guyatt transition rating items [26] to identify changes to a person’s health, which serve as an anchor for stability in the retest reliability analysis, as well as the PLUS-BHI items. The 2-day bladder symptom diary is mailed to the respondent independent of mode of PLUS-BHI completion. Up to 4 contact attempts are made for completion of the retest version of the PLUS-BHI and up to 3 contact attempts for completion of the 2-day bladder symptom diary. Respondents receive $10 compensation for completing each of the re-test and/or 2-day bladder symptom diary.

The NIDDK has an expectation of grant award recipients to support data sharing, facilitated by their data repository. To assess the impact of language related to data sharing in the consent process, each address is randomly assigned (1:1) to have the request for permission to share anonymized data with the NIDDK repository either at the end of the PLUS-BHI validation packet or to receive the request separately (e-mail for CASI, separate letter for PAPI). This allows for evaluation of potential threat bias influence on completion of the survey altogether and also the degree of endorsement separate from completion of the survey [23].

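### Chi-square and Fisher's exact test cannot measure test-retest agreement for categorical items with six or fewer response options

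*Protocol article*

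**What the plan says.** Aim (1), at the end of the article's Background, is to assess the reliability and validity of the instrument.

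The Analysis plan says that test–retest "reliability will be evaluated for all items comparing item response on initial PLUS-BHI completion to item response on retest version of PLUS-BHI". It then splits the items into two groups:

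- **Continuous items:** "Bland–Altman with 95% interval agreement threshold will be used for comparison of continuous variables". This group takes in longer response scales ("including categorical variables with greater than 6-point response options").
- **All other categorical items**, that is, those with six or fewer options: "and chi-square used for comparison of categorical variables", with Fisher's exact test where needed.

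The Analysis plan names no kappa, percent agreement, ICC or paired test. It states no significance level and no retention or removal rule for the retest result.

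Study administration, General population, describes how the retest arises. Women who complete the survey packet are re-contacted within 2 to 4 weeks and allocated 2:1 to a same-mode retest plus diary or to the diary alone. The retest form carries two Guyatt transition items, "which serve as an anchor for stability in the retest reliability analysis".

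**The concern.** A retest analysis has to show how closely each woman's second answer matches her first. Chi-square and Fisher's exact test can be applied to such data in two ways:

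- **(a) Independence in the test-by-retest table.** A significant result shows only that the two answers are not unrelated. Weak agreement is enough to produce it in a sample of this size, and a systematic shift in answers would produce it too.
- **(b) Equality of the test and retest distributions.** A non-significant result is then the reassuring one. Women answering at random from unchanged margins would give it almost every time. This use also treats paired answers as two independent samples.

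The wording leans towards (b): it speaks of comparison, and the next paragraph of the Analysis plan uses chi-square in that sense for mode of administration. The problem exists under both readings.

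At stake is the test-retest part of aim (1) for every categorical item with six or fewer options. The article does not say how many items fall in that group.

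**Working it through.** The plan gives no retest sample size, target coefficient or power, so there is no figure to reproduce. The check asks whether the named statistic separates reliable from unreliable items.

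**Inputs from the article**
- General population target: 694 completed surveys.
- Retest allocation 2:1, so the maximum retest n = 694 x 2/3 = 462.7, about 463.

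**Assumptions (not in the article)**
- Retest return of 100% (n = 463) or 50% (n = 231).
- Alpha 0.05, two-sided.
- Item margins: binary 70/30%; five categories 40/25/15/12/8%.
- The retest answer repeats the first with probability kappa and is otherwise an independent draw from the same margins.

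**Step 1. Raw agreement implied by kappa**

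Agreement = kappa + (1 − kappa) x Σp².
- Binary: Σp² = 0.49 + 0.09 = 0.58.
- Five categories: Σp² = 0.16 + 0.0625 + 0.0225 + 0.0144 + 0.0064 = 0.2658.
- Example, five categories at kappa 0.2: 0.2 + 0.8 x 0.2658 = 0.41.

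**Step 2. Significance threshold for a 2x2 item under reading (a)**

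Chi-square = n x phi², so p = 0.05 is reached at phi = √(3.841/n).
- n = 463: √(3.841/463) = 0.091.
- n = 231: √(3.841/231) = 0.129.

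With equal margins phi equals kappa, so an observed kappa of about 0.09 to 0.13 is already significant.

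**Step 3. Simulation, 2,000 runs per setting (each cell: binary / five-category)**

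| True kappa | Raw agreement | (a) significant, n = 463 | (a) significant, n = 231 | (b) not significant, n = 463 | (b) not significant, n = 231 |
|---|---|---|---|---|---|
| 0 | 58% / 27% | 5.5% / 4.8% | 5.0% / 3.8% | 94.4% / 94.8% | 95.3% / 95.6% |
| 0.1 | 62% / 34% | 55.4% / 74.4% | 32.1% / 42.0% | 96.1% / 97.2% | 96.5% / 97.1% |
| 0.2 | 66% / 41% | 99.5% / 100% | 85.6% / 96.9% | 96.9% / 97.7% | 97.2% / 98.4% |
| 0.4 | 75% / 56% | 100% / 100% | 100% / 100% | 98.8% / 99.5% | 99.1% / 99.6% |
| 0.7 | 87% / 78% | 100% / 100% | 100% / 100% | 100% / 100% | 99.9% / 100% |
| 0.9 | 96% / 93% | 100% / 100% | 100% / 100% | 100% / 100% | 100% / 100% |

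Under (a) at n = 463 the test result is essentially the same for kappa 0.2 and kappa 0.9. Under (b) it is much the same from kappa 0 to 0.9.

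**Step 4. Bland–Altman for items with more than six options**

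Half-width of the limits = 1.96 x SD x √(2(1 − r)). The last column comes from a simulated item rounded to 0–10 (assumed SD about 2.5, n = 463).

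| r | Differences inside the item's own limits | Half-width in SD units | Half-width, 0–10 item |
|---|---|---|---|
| 0 | 95.0% | 2.77 | 6.7 points |
| 0.2 | 95.0% | 2.48 | 6.0 points |
| 0.5 | 95.0% | 1.96 | 4.8 points |
| 0.9 | 95.0% | 0.88 | 2.3 points |

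The share inside the limits does not discriminate (94% to 97% for the rounded item). The width does.

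**The case against.** **The article is a condensed account, and the full protocol or SAP may say more.** This protects what is left out, such as an acceptable width for the Bland–Altman limits, a minimum coefficient, or the later reliability of scale scores that do not yet exist. It does not protect the categorical method, which the article names.

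**Bland–Altman is a recognised test-retest method.** This stands. A reader might infer that both planned methods fail, or that the 95% threshold is met automatically. The documents do not support that. The limits measure agreement in item units and their width separates good items from poor ones. The threshold is met by construction only if it means the share of differences inside the item's own limits, which is one reading of an unclear sentence.

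**No retest pass rule is stated, and other screens exist.** This also stands. The Analysis plan filters items on floor and ceiling effects, non-response, factor loadings and Cronbach's alpha. An item answered at random would be unlikely to load on any dimension. These screens do not measure stability over time, however, so they do not replace a retest statistic.

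**The transition items are already planned.** They help select stable women but do not quantify agreement.

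**The simulated rates rest on assumptions.** They do: at kappa 0.1, reading (a) is significant in 55% to 74% of runs at n = 463 but in 32% to 42% at n = 231. The conclusion does not depend on them, because neither null hypothesis concerns agreement.

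**Conclusion.** The concern holds for categorical items with six or fewer response options. Chi-square or Fisher's exact test on paired test and retest answers does not quantify agreement, so the planned analysis cannot identify unreliable items in this group or support the test-retest part of aim (1) for them. The percentages depend on the assumed margins, alpha and retest return. In addition, 463 is an upper bound that falls with non-return and with restriction to stable women.

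Two stronger conclusions should not be drawn. The first is that unreliable items will pass and enter the scale: no retest removal rule is stated and other item screens apply. The second is that any claim of reliability would be unsupported: internal consistency is assessed separately. For items with more than six options the point is only one of clarification, namely what the 95% threshold refers to.

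**What to change.** - **Items with six or fewer options:** replace chi-square and Fisher's exact test in the retest analysis with weighted kappa for ordinal items (weights stated) and unweighted kappa for nominal items. Give each with a 95% confidence interval and percent agreement alongside.
- **Analysis set:** use the women rated stable on the two Guyatt items already in the retest form.
- **Items with more than six options:** keep Bland–Altman. Either add an absolute-agreement ICC with a 95% confidence interval, or compare the limits with a pre-set acceptable width rather than counting differences inside the item's own limits.

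The cost is analysis work and a change of wording. Kappa comes from the same paired answers that the plan already collects, so sample size, allocation and forms do not change. The article describes recruitment as still under way.

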**Methods:**

Three samples of women are being recruited: a sample from a nationally representative general population and two locally recruited clinical center samples—women with a targeted range of symptom severity and type, and a postpartum group. The general population sample includes 694 women, 18 years or older, randomly selected from a US Postal delivery sequence file. Participants are randomly assigned to electronic or paper versions of the bladder health instrument along with a battery of criterion questionnaires and a demographic survey; followed by a retest or a two-day voiding symptom diary. A total of 354 women around 7 clinical centers are being recruited across a spectrum of self-reported symptoms and randomized to mode of completion. They complete the two-day voiding symptom diary as well as a one-day frequency volume diary prior to an in-person evaluation with a standardized cough stress test, non-invasive urine flowmetry, chemical urine analysis and post void residual measurement. Independent judge ratings of bladder health are obtained by interview with a qualified health care provider. A total of 154 postpartum women recruited around 6 of the centers are completing similar assessments within 6–12 weeks postpartum. Dimensional validity will be evaluated using factor analysis and principal components analysis with varimax rotation, and internal consistency with Cronbach’s alpha. Criterion validity will be assessed using multitrait-multimethod matrix including correlations across multiple data sources and multiple types of measures.

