#### General population

The US Postal delivery sequence file (DSF), an address-based sample frame, is used to draw a random nationally representative sample. The DSF is the gold standard for address based sampling of US households with low coverage error [23]. In order to have geographic representation in terms of region of the country and across urban and rural continuum, a stratified sampling strategy was implemented with three nested sampling unit levels: primary sampling unit (PSU), secondary sampling unit 1 (SSU1) and a secondary sampling unit 2 (SSU2). The primary sampling unit mimics the PSU groupings used by the National Health And Nutrition Examination Survey (NHANES), [24] with states aggregated into one of five strata based on state health indicators. Each PSU is further divided between 0 and 2 times based on general geographic proximity (e.g., East, Midwest and West) resulting in a total of 11 SSU1 strata across the 5 PSUs (Table 2).

**Table 2 Tab2:** General population sampling SSU1 state grouping

SSU1 state grouping	States included
Group 1: PSU 1, West	HI, UT, WA
Group 2: PSU 1, Midwest	IA, MN, ND
Group 3: PSU 1, East	CT, MA, NH, NJ, NY, VT, RI
Group 4: PSU 2, CA	CA
Group 5: PSU 3, West	AK, AZ, CO, ID, MT, NM, OR, WY
Group 6: PSU 3, Midwest	IL, KS, ME, NE, SD, WI
Group 7: PSU 3, South	FL, VA
Group 8: PSU 4, TX	TX
Group 9: PSU 4, East	DE, IN, MD*, MI, OH, PA
Group 10: PSU 5, Western South	AR, LA, MO, NV, OK
Group 11: PSU 5, Eastern South	AL, KY, GA, MS, NC, SC, TN, WV

^*^DC counted in MD

PSU, Primary sampling unit; SSU, Secondary sampling unit

Each of the 11 SSU1 were further stratified as SSU2 according to the rural urban continuum codes (RUCC). These RUCC were categorized into four groups: urban (RUCC 1 and 2), suburban (RUCC 3, 4 and 6), rural city (RUCC 5 and 7), and rural (RUCC 8-9). A total frame of 6000 households (for a target of approximately 694 completed validation surveys) is randomly selected across sampling strata. Sampling is proportional across SSU1 state groupings, and equal across the 4 RUCC groups for a total of 44 sampling strata (Table 2).

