#### Clinical center populations

The general clinical center population of women are being recruited from the community and medical practices surrounding the PLUS clinical research centers: Loyola University Chicago, University of Alabama at Birmingham, University of California San Diego, University of Michigan, University of Pennsylvania, Washington University in St Louis, and Yale University. Potential participants are screened on inclusion/exclusion criteria (Table 1) and purposive sampling conducted with the intention of representing the spectrum of bladder health and LUTS. To accomplish this, a modified version of the Patient Perception of Bladder Condition (PPBC) questionnaire is used to categorize participants into one of four equal size groupings [25]. Using the question “Which of the following statements best describes any problems you may have with peeing or your bladder?”: women are screened into healthy with no reported problems (PPBC response = 1), mild bladder problems (PPBC response = 2 or 3), moderate bladder problems (PPBC response = 4), or severe bladder problems (PPBC response = 5 or 6). When a quota is full (i.e., severe), individuals are screened out (Table 3).

**Table 3 Tab3:** VIEW target enrollment of clinical center population bladder symptom strata

Symptom strata	Self-report of LUTS-PPBC				
	Healthy	Mild	Moderate	Severe	Total
Frequency	90	15	15	15	45+
Incontinence		15	15	15	45+
Urgency		15	15	15	45+
Pain/discomfort		15	15	15	45+
Peeing/flow		15	15	15	45+
Urinary tract infection		15	15	15	45+
Total	90	88	88	88	354

LUTS, Lower urinary tract symptoms; PPBC, Patient perception of bladder condition: The four categories of Healthy to Severe map to PPBC responses to the question “Which of the following statements best describes any problems you may have with peeing or your bladder?”: healthy with no reported problems (PPBC response = 1), mild bladder problems (PPBC response = 2 or 3), moderate bladder problems (PPBC response = 4), or severe bladder problems (PPBC response = 5 or 6)

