While the goal of the PLUS-BHS is to be used across the female lifespan including adolescent girls and adult women, this initial validation was limited to English speaking women ≥ 18 years of age. The development of a similar instrument for adolescents and Spanish speaking females is underway and will be facilitated by the outcomes of the VIEW study. Since the instrument is specifically designed for women, who have different lower urinary tract anatomy and symptoms when compared to men or transgender women, this instrument is not intended for use with males or adolescent females. Lastly, the PLUS-BHI is only tested for clinical research in ambulatory women; thus, women who have functional and neurogenic LUTS are not included in the spectrum of bladder health assessed by the PLUS-BHI. The questions and answer stems might not be appropriate in this population and would need further testing to determine their ability to discriminate bladder health from bladder disease in certain populations.

The VIEW study includes women from the general population and from those recruited around clinical centers, those who are recently postpartum and who attend clinical practices for health care. While this range of recruitment can be a strength of the study to assure a wide range of contexts, it is also possible that the distribution of bladder health may not be comparable between the populations. While clinical center recruitment was intentionally designed in order to capture the full spectrum of very healthy to very unhealthy, the screening instrument we used (the PPBC) may not accurately discriminate across the true severity of disease and does not address impact of symptoms. Similarly, validated questionnaires were not used to stratify women according to type of LUTS for inclusion in the clinical examination. It is also possible that women recruited from clinical practices, specifically specialty practices (e.g. urology, urogynecology) and with self-reported severe symptoms may be fundamentally different than women who may have symptoms but who do not seek out care for LUTS. As a result, the PLUS-BHS may discriminate between participants with similar LUTS who have different expectations for their bladder health. Modifications to the scoring of the PLUS-BHS may need to be made for general, clinical and postpartum populations and the PLUS-BHS would not be as generalizable as desired.

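### Flagging items for removal because raw responses differ between samples preferentially targets the items that best track bladder health, since the clinical sample is recruited on bladder condition

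*Protocol article*

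**What the plan says.** The Analysis plan compares item responses by mode, between and within the general and clinical samples, using Tukey's HSD or chi-square (Fisher's test where needed). It then states: "Items demonstrating significant differences across mode of administration or across sample will be considered for removal". No conditioning on the level of bladder health is attached to the across-sample part.

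The samples are recruited in different ways:

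- **General population.** A random draw from the postal delivery file, stratified by state group and rural-urban code, with "a target of approximately 694 completed validation surveys". Nothing in the selection depends on bladder health.
- **Clinical centers.** Here there is "purposive sampling conducted with the intention of representing the spectrum of bladder health and LUTS". A single screening question (modified PPBC) serves to "categorize participants into one of four equal size groupings", and the quotas bind: "When a quota is full (i.e., severe), individuals are screened out". Table 3 sets 90 healthy, 88 mild, 88 moderate and 88 severe. A second screen covers frequency, urgency, incontinence, pain and voiding difficulty.

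Under Strengths and limitations the article concedes that "it is also possible that the distribution of bladder health may not be comparable between the populations". Later in the Analysis plan, factor structures are to be compared across mode and sample.

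**The concern.** A raw difference between two groups on an item can mean that the item behaves differently in the groups, or that the groups differ on what the item measures. Only the first is a defect. Where one group is recruited by quota on bladder condition and the other is not, the second explanation is the expected one. A difference of that kind is known-groups evidence in the item's favour.

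The across-sample limb cannot tell the two apart, and the better an item tracks bladder health, the more likely it is to be flagged. The aim is a scale that covers the whole range of bladder health. Item screening is described ahead of the factor analysis, the internal-consistency work and the multitrait-multimethod matrix, so a discriminating item lost at that stage is lost to all of them.

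**Working it through.** **1. The plan's figure.** Table 3: 90 + 88 + 88 + 88 = 354, as stated. Women with a problem by quota: 3 × 88 = 264, and 264/354 = 74.6%.

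**2. Inputs.** n = 694 (general) and 354 (clinical), from the article. *Assumed*: two-sided α = 0.05, as no level is stated for the item tests; the latent shift d; the item loadings λ; and the general-population prevalence of problems. The article gives none of these, so ranges are shown.

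**3. Continuous items.** SE = √(1/694 + 1/354) = 0.0653 SD. The difference detectable with 80% power is (1.96 + 0.84) × 0.0653 = 0.18 SD. An item with loading λ shifts by λd, so P(flag) ≈ Φ(λd/SE − 1.96). For example, with λ = 0.4 and d = 0.5: 0.20/0.0653 = 3.06, and Φ(1.10) = 0.865.

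| Latent shift | λ = 0.2 | λ = 0.4 | λ = 0.6 | λ = 0.8 |
|---|---|---|---|---|
| 0.2 SD | 8.9% | 23.1% | 45.1% | 68.8% |
| 0.3 SD | 14.9% | 45.1% | 78.7% | 95.7% |
| 0.5 SD | 33.4% | 86.5% | 99.6% | 100% |

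None of these items is biased between samples. The flag rate simply rises with loading.

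**4. Binary items.** Let p_G be the general-population prevalence of any problem and p_C = 0.746. An item with Youden index J (sensitivity equal to specificity) differs by J × (p_C − p_G). P(flag) ≈ Φ((difference − 1.96·SE₀)/SE₁), with SE₀ pooled and SE₁ unpooled.

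- Perfect item (J = 1): over 99.9% at p_G = 30% to 50%, 99.8% at 60%, 89% at 65%, 34% at 70%.
- p_G = 50%, J = 0.1, 0.3, 0.5, 0.7: 11%, 62%, 97%, 100%.
- p_G = 60%, same J: 6.5%, 27%, 62%, 90%.

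The gradient with item quality is the same. Its size depends on how far p_G lies below 74.6%.

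**5. Conditioning on bladder health.** In a simulation (400 replicates, 694 vs 354, unbiased items), the raw test at d = 0.5 flagged 34%, 86%, 100% and 100% for loadings 0.2 to 0.8, agreeing with step 3. Adding latent bladder health to the comparison brought flagging to about 4% to 6% at every loading, for shifts of 0.3, 0.5 and 0.8. The simulation conditioned on the true latent value; a score measured with error would do somewhat less well.

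**The case against.** **It is only a flag.** The Analysis plan separates firm rules (over 85% of responses in the tail, alpha below 0.4) from softer ones that call for consideration, and this is a soft one. Two investigators then compare and discuss factor results. This stands: the document does not say that flagged items are dropped. But no criterion is given for keeping a flagged item, and a screen whose signal rises with item quality is a poor basis for discretion.

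**The sentence may mean something else.** Its paragraph opens on mode, so the across-sample part could refer to mode effects that vary by sample. As written, however, sample is a separate ground, joined by *or*. If the narrower meaning was intended, the text should say so.

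**The size is not known.** This stands. A reader might infer that every valid item must differ, or that nearly all would be flagged. The documents do not support that. General-population bladder health is not reported, and even a perfect item is flagged only 34% of the time at an assumed prevalence of 70%. The 74.6% comes from one global question. By symptom type, Table 3 fixes only a floor of 45 women (45/354 = 13%), so the design guarantees no large difference on any single symptom. The authors also doubt how well the PPBC separates severity.

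**Sample differences are already handled.** The factor-structure comparison and the stated limitation show that the authors are aware of them. Neither alters the item rule.

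**What about mode?** A reader might extend the criticism to the mode limb, on grounds of multiplicity, low power or non-significance taken as equivalence. That does not hold. Mode is randomised in the general and general clinical samples, so a raw comparison is legitimate there. Error level, adjustment and margins are details that an article leaves to the full plan. The clinical contrast alone (118 vs 236) would miss d = 0.2 57% of the time, but the general sample is tested too. If its 694 completers split 347/347 or 231/463 (assumed), power there is 75% or 70%. With independent samples and a common effect, both contrasts miss it only 0.57 × 0.25 = 14% to 0.57 × 0.30 = 17% of the time. Nowhere does the text equate non-significance with mode equivalence.

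**Conclusion.** The across-sample limb is a misdirected screen. Whenever bladder health differs between the quota-filled clinical sample and the unselected general sample, it flags the more discriminating items more often: from 33% at loading 0.2 to 100% at 0.8 for an assumed 0.5 SD shift, and from 15% to 96% for 0.3 SD.

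The direction needs only that the two distributions differ, which the article itself allows for. The size rests on assumed shifts, loadings, prevalence and α = 0.05. If Tukey's HSD is applied over more than two groups, flag rates fall somewhat but the gradient remains. The effect fades as general-population prevalence nears 75%.

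The documents do not show that the scale will lose discrimination, because flagged items may be kept. The point does not extend to randomised mode. Severity: SHOULD-FIX.

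**What to change.** In the Analysis plan, remove raw difference between samples as a ground for removal. For example:

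> Items whose responses differ by randomised mode will be considered for removal. Raw differences between samples will be reported as known-groups evidence and are not a ground for removal. Once dimensions are identified, comparability across samples will be assessed conditional on bladder health, by differential item functioning or measurement invariance, with a pre-set effect size for flagging.

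If the intended meaning was mode effects that vary by sample, state that instead, as a mode-by-sample interaction.

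The conditional test belongs after dimensions are identified. Before that, the item pool branches and is probably multidimensional, so a total or rest score would be a doubtful matching variable. This order also fits the planned comparison of factor structures.

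Cost: analysis wording and modest programming, with no new data. The downside is that a matching variable and an effect-size threshold must be agreed in advance.
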